### Strategies to improve adherence to interventions {11c}

During the RCT, participants will receive an incentive of reduced costs for euploid embryo tests.

### Relevant concomitant care permitted or prohibited during the trial {11d}

Any treatment or change outside of the study intervention will be monitored throughout the trial.

### Provisions for posttrial care {30}

No special provisions are offered.

### Outcomes {12}

#### Primary outcome measure

The primary outcome measure is the euploid embryo rate: the ratio of the euploid embryos to the number of mature oocytes.

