Emerging evidence implicates the mevalonate (MVA) pathway—a central metabolic route in cholesterol biosynthesis—in the regulation of meiotic maturation and genomic stability. As the primary regulator of cholesterol homeostasis, which undergoes age-related alterations [8], the MVA pathway supports oocyte maturation partly through luteinizing hormone receptor (LHR) and epidermal growth factor (EGR) signaling. Our prior investigations identified a marked suppression of MVA-related gene activity in granulosa cells from AMA patients compared to younger counterparts [8]. In animal models, exogenous MVA compounds have shown promise in correcting meiotic abnormalities and reducing aneuploidy rates in aging oocytes [8]. However, despite these mechanistic insights and preclinical data, the effect of MVA supplementation on euploid blastocyst formation in women of AMA remains unknown.

Given the potential role of MVA in restoring oocyte quality and the lack of effective interventions for women of AMA, this study proposes a randomized controlled trial to evaluate MVA supplementation during the pre-fertilization phase in women aged 38–42 undergoing PGT-A cycles, thereby facilitating clinical translation and potential integration into ART practice.

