### Intervention description {11a}

A total of 150 PGT-A cycles will be included in the study. All retrieved COCs from each cycle will be randomly allocated into two parallel groups: the MVA supplementation group (intervention group) and the standard control group. Randomization will be performed at the level of sibling oocytes to minimize inter-individual variability.

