#### Intervention group

COCs assigned to the intervention group will be incubated in fertilization medium supplemented with MVA metabolites at a concentration of 50 µM for 4 h prior to insemination. Following this exposure, all subsequent embryo culture procedures will be conducted according to standard IVF/ICSI protocols.

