## Assignment of interventions: allocation

### Sequence generation {16a}

All oocytes retrieved in each cycle will be evenly distributed into two fertilization dishes (Dish 1 and Dish 2). If an odd number of oocytes is retrieved, the extra oocyte will be placed in Dish 1. The randomization will be performed using SAS 9.4 statistical software, applying a completely randomized method.

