## Statistical methods

### Statistical methods for primary and secondary outcomes {20a}

Data analysis will be conducted using SPSS version 13.0. Descriptive statistics will summarize baseline demographic and clinical characteristics. Categorical variables—including clinical pregnancy rate, implantation rate, and miscarriage rate—will be compared between groups using the chi-square (*χ*^2^) test or Fisher’s exact test where appropriate. Continuous variables such as patient age, baseline FSH levels, antral follicle count (AFC), total gonadotropin dosage and duration, number of oocytes retrieved, and fertilization rate will be analyzed using independent-samples *t*-tests or nonparametric equivalents as appropriate. To account for potential confounding factors, multivariable regression analyses will be conducted. Logistic regression models will be applied for binary outcomes (e.g., clinical pregnancy, implantation, miscarriage), while linear regression will be used for continuous outcomes (e.g., number of mature oocytes, fertilization rate). Models will adjust for maternal age, baseline FSH levels, AFC, ovarian stimulation parameters, and other relevant covariates. For pregnancy outcomes, paternal factors such as age and semen parameters will also be included as covariates. A two-sided *p*-value < 0.05 will be considered statistically significant. Effect sizes will be reported with 95% confidence intervals. Sensitivity analyses will be conducted to test the robustness of the results.

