### Methods in analysis to handle protocol nonadherence and any statistical methods to handle missing data {20c}

Data will be analyzed following the ITT principle. Missing data will be analyzed. The imputation of missing values is not intended, although multiple imputations might be used within sensitivity analyses assuming data are missing at random.

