The primary endpoint, euploidy efficiency (euploid blastocysts per mature oocyte), was selected because it directly reflects meiotic fidelity and genomic stability. Secondary endpoints, including clinical pregnancy and live birth rates, were included to capture downstream clinical implications and to assess the potential translational impact of the intervention.

Several limitations should be acknowledged. First, it is open-labeled as the MVA-supplemented and standard media cannot be blinded; although this may introduce bias, the use of standardized procedures and an objective genomic endpoint minimizes subjectivity. Second, as a single-center trial, the generalizability of findings may be limited, though the intervention is simple and easily replicable. Third, the choice of euploidy efficiency as a surrogate endpoint enables feasibility with a smaller sample size but may not fully reflect clinical outcomes; therefore, pregnancy and live birth are included as secondary endpoints. Operational challenges include slow recruitment due to diminished ovarian reserve, strict standardization of intervention procedures, and potential attrition or missing data. These will be addressed through extended recruitment, detailed SOPs with staff training, and intention-to-treat analyses with retention strategies.

If effective, MVA supplementation could serve as a simple, low-cost upstream intervention that can be seamlessly integrated into standard IVF/ICSI protocols, potentially improving embryo usability and pregnancy outcomes in women of AMA. Scientifically, the trial will provide the first human evidence supporting the role of the MVA pathway in oocyte meiotic fidelity, thereby advancing understanding of reproductive aging mechanisms. Future research should investigate dose-response relationships, assess applicability in other populations such as younger women with diminished ovarian reserve, and conduct multicenter randomized trials powered for live birth outcomes to validate and extend these findings.

In summary, this trial evaluates a biologically grounded and operationally feasible intervention addressing the root cause of embryo aneuploidy in AMA. The results will inform both clinical practice and basic science, guiding next steps in optimizing fertility care for women of AMA.

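### The primary rate divides by mature oocytes, which appear to be identified after allocation and which MVA may change, so it does not cover all allocated COCs and can depart from euploid yield

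*Protocol article*

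**What the plan says.** - **Allocation.** Intervention description {11a}: "All retrieved COCs from each cycle will be randomly allocated into two parallel groups". Sequence generation {16a} splits all oocytes retrieved in a cycle evenly between two dishes. Neither section selects on maturity first.
- **Exposure.** COCs in the intervention arm are "incubated in fertilization medium supplemented with MVA metabolites at a concentration of 50 µM for 4 h prior to insemination".
- **Primary outcome.** Outcomes {12}: "the ratio of the euploid embryos to the number of mature oocytes". Sample size {14} and the Discussion use the same denominator.
- **Mechanism.** Background and rationale {6a}: "the MVA pathway supports oocyte maturation partly through luteinizing hormone receptor (LHR" and growth-factor signalling. The Discussion repeats the link to meiotic maturation.
- **Maturity as an outcome.** Statistical methods {20a}: "linear regression will be used for continuous outcomes (e.g., number of mature oocytes, fertilization rate".
- **Objective and principle.** Objectives {7} asks about the yield of euploid embryos. Section {20c} says: "Data will be analyzed following the ITT principle".
- **Interpretation.** The Discussion says that the endpoint "was selected because it directly reflects meiotic fidelity and genomic stability".

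**The concern.** Randomisation makes the two sets of COCs comparable. It does not make the two sets of mature oocytes comparable if treatment can influence which oocytes are counted as mature. A ratio with mature oocytes underneath can then move when euploid embryos per treated COC do not, or stay still when they do. A reader who takes the primary result as the answer to the yield objective could be misled in either direction.

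A related point concerns interpretation. Euploid blastocysts per mature oocyte is the product of fertilisation, development to a biopsied blastocyst, and the euploid share among those blastocysts. It can rise through the first two with no change in the third, so it is not a direct measure of meiotic fidelity.

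**Working it through.** **1. The plan's own figures.** Inputs from Sample size {14}: 10% against 17%, α 0.05 (two-sided in {20a}). Power is not stated; 80% is assumed because it reproduces the result.

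n = (1.960 + 0.842)² × (0.10×0.90 + 0.17×0.83) / 0.07² = 7.849 × 0.2311 / 0.0049 = 370.2, so 371 per group. Then 371 × 1.1 = 408, and 816 / 5.45 = 149.7, about 150 cycles. The sample size uses the same denominator as the endpoint, so its arithmetic is not at fault here.

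**2. How the ratio responds to maturity.** Let *m* be the fraction of allocated COCs with a mature oocyte and *y* the euploid blastocysts per allocated COC. The primary rate is *y/m*. The article gives no value for *m*, so 75% and 80% in control and shifts of ±10 points are assumptions. Hold *y* equal in both arms, at 0.10 × control maturity:

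| Control *m* | *y* in both arms | MVA *m* | Primary rate, MVA | Control |
|---|---|---|---|---|
| 0.75 | 0.075 | 0.85 | 0.075/0.85 = 8.8% | 10% |
| 0.80 | 0.080 | 0.90 | 0.080/0.90 = 8.9% | 10% |
| 0.75 | 0.075 | 0.65 | 0.075/0.65 = 11.5% | 10% |
| 0.80 | 0.080 | 0.70 | 0.080/0.70 = 11.4% | 10% |

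**3. Effect on the test.** Take 408 control mature oocytes and 408 × *m*(MVA)/*m*(control) in the MVA arm. Use a two-sided 5% test of two proportions with oocytes treated as independent, as in the plan's own calculation.

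- *No true difference per COC, maturity rises.* The chance of falsely declaring MVA superior is about 0.5–0.6%, below the nominal 2.5%. The bias runs against MVA.
- *No true difference per COC, maturity falls.* The chance of falsely declaring MVA superior is about 9–10%.
- *True 1.7-fold gain per COC, maturity rises.* The rate in the MVA arm is 0.1275/0.85 = 15.0% or 0.136/0.90 = 15.1%. Power is 60–62%.
- *True 1.7-fold gain per COC, maturity falls.* The rate is 0.1275/0.65 = 19.6% or 0.136/0.70 = 19.4%. Power is about 96%.

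**4. Price of a per-COC analysis.** With equal maturity, 408 mature oocytes correspond to 408/0.75 = 544 or 408/0.80 = 510 COCs per arm. Power for 7.5% against 12.75%, or for 8.0% against 13.6%, is about 82%. The same effect per mature oocyte has 83.4%. Over control maturity of 70–85% the per-COC power is 81.7–82.5%, so the loss is about 1–2 points.

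**The case against.** Several points on the other side stand.

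- **Timing is inferred.** No section says when maturity is scored. That it follows exposure is inferred from the randomisation and exposure of all retrieved COCs. Sample size {14} speaks only of mature oocytes retrieved, when it describes the centre's historical rate.
- **An effect on maturity is hypothesised, not shown.** A reader might infer that the denominator is affected by treatment. The article does not support that: the animal results it cites concern meiotic errors and aneuploidy, and nothing shows that four hours of MVA changes the mature fraction. The bias may be nil.
- **The intention-to-treat principle is not shown to be broken.** A reader might infer that it is. No section analyses an oocyte outside its allocated arm, and the denominator is used consistently in the endpoint, the sample size and the Discussion. This is a debatable choice of estimand, not a contradiction.
- **The hypothesised direction is conservative.** If MVA raises maturity, the ratio works against MVA. A false success needs MVA to lower maturity, contrary to the rationale. What remains in the hypothesised direction is lost power.
- **The scenario is extreme.** Holding yield per COC fixed while maturity moves means that the gained or lost mature oocytes contribute no net euploid embryos.
- **Some of this may be planned elsewhere.** Section {20a} already models the number of mature oocytes and promises sensitivity analyses, and a condensed article may leave a supportive analysis to a fuller document. The denominator, the yield objective and the intention-to-treat statement are nevertheless fixed in this text, and the mismatch lies between them.

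**Conclusion.** The point holds in a limited form. The protocol randomises all retrieved COCs but compares the arms on a subset that appears to be determined after allocation, and that its own rationale and outcome list treat as open to influence by MVA. The stated comparison therefore does not cover all allocated COCs and may differ from the effect on euploid yield. Size and direction are unknown. Under the assumed maturity figures, the distortion is about −1.1 to −1.2 points (8.8–8.9% against 10%) or +1.4 to +1.5 points (11.4–11.5% against 10%), set against a target difference of 7 points. If maturity rises, the main cost is power: about 60–62%, against 82% per COC. These figures rest on maturity fractions that the article does not give and on independent oocytes.

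The claim that the ratio directly reflects meiotic fidelity is too strong, although the Discussion does acknowledge that the endpoint is a surrogate. This is an inexpensive improvement and not a reason to replace the endpoint.

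**What to change.** - Keep euploid blastocysts per mature oocyte as the primary endpoint.
- In {12}, state when maturity is assessed relative to allocation and exposure.
- In {20a}, add an intention-to-treat analysis of euploid blastocysts per COC allocated to each dish, with the same model as the primary analysis. Date it, and declare that it was added before the analysis was unblinded. Under {17a} the statisticians are blinded to grouping, and Trial status places submission before the end of data analysis.
- Report by arm: mature oocytes per COC, blastocysts per mature oocyte, and euploid per biopsied blastocyst.
- If the two analyses disagree, qualify any conclusion of superiority. Do not make superiority depend on the per-COC confidence interval. That would turn the added analysis into the deciding test after the last biopsy in January 2025.
- In the Discussion, drop the wording that the ratio directly reflects meiotic fidelity, and interpret fidelity with the euploid proportion among biopsied blastocysts.

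Cost: one more model and one table, from data that should already be recorded. The per-COC analysis has about 1–2 points less power; the primary analysis loses none.

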#### Secondary outcome measures

Secondary outcome measures are the clinical pregnancy rate, miscarriage rate, and live birth rate.Clinical pregnancy rate: The ratio of the clinical pregnancy (intrauterine gestation sac with a fetal heart beat) number to the number of patients who received embryo transferMiscarriage rate: The ratio of the number of nonviable pregnancies before 28 weeks of gestation to the number of clinical pregnanciesLive birth rate: The ratio of the number of normal fetuses delivered after 28 weeks of gestation to the number of patients who received embryo transfer

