**Discussion:**

This trial is expected to evaluate the effects of MVA supplementation on euploidy blastocyst rate and clinical pregnancy outcomes in women of AMA undergoing PGT-A. These findings may provide valuable insights into the potential application of MVA supplementation as an adjunct treatment for infertility in this population.

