### Trial design {8}

This is a single-center, prospective, randomized, within-subject controlled superiority trial with a theoretical 1:1 allocation of cumulus-oocyte complexes (COCs) to intervention vs. control.

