## Interventions

### Explanation for the choice of comparators {6b}

The standard control will consist of oocytes from the same individual that were cultured under routine IVF/ICSI laboratory conditions without MVA supplementation. This comparator represents the current standard of care in IVF/ICSI laboratory practice and allows for a direct evaluation of the effect of MVA treatment under otherwise identical conditions. By randomly allocating oocytes from the same patient into intervention and standard control groups, the design minimizes inter-individual variability and thereby enhances the internal validity of the study.

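### Pregnancy outcomes are compared between groups per woman transferred, but sibling oocytes were randomized, so the comparison is not a randomized one

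*Protocol article*

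**What the plan says.** **Design.** Trial design {8} describes a "randomized, within-subject controlled superiority trial with a theoretical 1:1 allocation of cumulus-oocyte complexes (COCs) to intervention vs. control". Under Intervention description {11a}, "All retrieved COCs from each cycle will be randomly allocated into two parallel groups", and "Randomization will be performed at the level of sibling oocytes to minimize inter-individual variability". Sequence generation {16a} agrees: "All oocytes retrieved in each cycle will be evenly distributed into two fertilization dishes (Dish 1 and Dish 2"). The comparator section {6b} justifies the design in the same terms ("By randomly allocating oocytes from the same patient into intervention and standard control groups"), and the main Discussion repeats it. The one exception is the Abstract's Methods paragraph, which has women randomized to one group or the other.

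**Outcomes.** Secondary outcome measures in {12} relates clinical pregnancies "number to the number of patients who received embryo" transfer. Live birth has the same denominator. Miscarriage is taken per clinical pregnancy.

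**Analysis.** Section {20a} lists "clinical pregnancy rate, implantation rate, and miscarriage rate" among the categorical variables to be compared between groups by chi-square or Fisher's exact test, with covariate-adjusted logistic regression for binary outcomes. Live birth is not in that list, although the list is introduced as inclusive. Section {20c} invokes intention to treat.

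**Conclusion promised.** The Abstract's Discussion says the trial will "evaluate the effects of MVA supplementation on euploidy blastocyst rate and clinical pregnancy outcomes".

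**The concern.** A between-group test on women needs each woman to belong to a group, and here none does. A label can only be supplied afterwards, from the dish that produced the transferred embryo. Randomization did not fix that label. It exists only if the dish yielded a transferable embryo, which is close to the primary outcome itself.

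A p-value from such a test would be read as a randomized effect of MVA on pregnancy, and the Abstract invites that reading. In fact it would compare two sets of women selected by what happened after randomization. A larger sample would not cure this.

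**Working it through.** **1. Reproduce the protocol's own figure.** Inputs from Sample size {14}: 10% versus 17% euploid blastocysts per mature oocyte, alpha 0.05 (two-sided per {20a}), 10% dropout, 5.45 mature oocytes per cycle. Power is not stated; 80% is assumed.

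- Per group, unpooled variance: (1.960 + 0.842)² × (0.10×0.90 + 0.17×0.83) / 0.07² = 370.2, rounded up to 371, as stated.
- Dropout: 371 × 1.1 = 408.1, stated as 408.
- Cycles: 2 × 408 / 5.45 = 149.7, stated as about 150.

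This calculation takes the oocyte as its unit. It says nothing about women transferred.

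**2. How many cycles could supply a transfer from each dish?** Assumptions: an even split of mature oocytes, independent oocytes, and only euploid blastocysts transferred. Mature oocytes per dish: 5.45 / 2 = 2.725.

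| Euploid blastocyst from | Probability per cycle | Of 150 cycles |
|---|---|---|
| Control dish | 1 − 0.90^2.725 = 0.250 | about 37 |
| MVA dish | 1 − 0.83^2.725 = 0.398 | about 60 |
| Both dishes | 0.250 × 0.398 = 0.099 | about 15 |
| At least one dish | 0.250 + 0.398 − 0.099 = 0.548 (unrounded inputs) | about 82 |
| Neither dish | 1 − 0.548 = 0.452 | about 68 |

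Of the roughly 82 cycles with any euploid embryo, about 67 (82 − 15) have one from a single dish only. The two denominators differ because of the assumed treatment effect itself.

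**3. Sensitivity.** A simulation with Poisson oocyte counts and a between-woman logit standard deviation of 0, 0.5 or 1.0 gives 34–37 control, 52–57 MVA, 16–18 both and 68–78 with at least one. The counts shift, but the pattern does not.

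**4. What fixes a woman's label?**

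- Only one dish yields a euploid embryo: the label is determined by the primary outcome.
- Both dishes do (about 15 cycles): the article states no rule that fixes the label, and section {17a} says patients and researchers know the assignments.
- Neither does (about 68 cycles): under the euploid-only assumption the cycle leads to no transfer and drops out of the comparison.

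In none of these cases was the woman randomized to the label she carries. An intention-to-treat analysis per woman is therefore undefined.

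**The case against.** **What stands on the other side.** These are secondary outcomes. The primary endpoint, its allocation and its sample size do not depend on them. The main Discussion concedes that the primary endpoint is a surrogate and calls for later trials powered for live birth. That caveat concerns power and surrogacy, however, and does not tell the reader that the clinical comparison is non-randomized. The adjustment in {20a} for maternal age, FSH, AFC, stimulation and paternal factors may remove some differences between women, but it does not restore randomization.

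**Stronger readings that the documents do not support.**

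- *Staff who know the arm choose the embryo.* The article does not say who chooses or how. A selection rule may stand in the full protocol, which is not shown. Even if choice were biased, it could act in only about 15 of 150 cycles. The main problem is the single-dish cycles.
- *Only euploid embryos are transferred.* The background section and the order of steps in Table 1 imply this, but no rule states it.
- *Live birth is explicitly tested between groups.* Section {20a} does not name it. It comes in only through the inclusive wording, although its denominator in {12} has the same defect.
- *Finding no difference per transfer would be an error.* If MVA only raises the yield of euploid embryos, no difference per transfer is the right answer to that question, and the primary outcome captures the gain.
- *The bias can be put at about 20 percentage points.* At an assumed 50% pregnancy rate, 37 versus 60 gives a 95% half-width of 1.96 × √(0.25/37 + 0.25/60) = 0.205. That measures imprecision and also counts the dual-dish cycles twice. Nothing in the documents allows the selection bias to be quantified.
- *The main Discussion promises a randomized clinical effect.* It speaks of downstream implications and translational impact. The wording about effects on pregnancy outcomes is in the Abstract.

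**Conclusion.** The concern holds as a should-fix point on secondary outcomes. The sections on design, comparator, intervention and sequence generation, and the main Discussion, all place each woman's oocytes in both arms. The Abstract's sentence to the contrary must be reconciled with them. The planned between-group comparison of clinical pregnancy and miscarriage, and presumably live birth, is therefore not protected by randomization.

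The size is structural: about 37 control and 60 MVA cycles with a transferable embryo and about 15 with both, out of 150. It rests on the rates in {14}, independence, an even split and euploid-only transfer. These are counts of cycles, and the Abstract gives 128 women for about 150 cycles, so counts of women may be lower. Neither the direction nor the amount of bias is established. The primary comparison is not affected by this point.

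**What to change.** - In {12} and {20a}, state that clinical pregnancy, miscarriage and live birth are descriptive and non-randomized. Report them by source dish of the transferred embryo, with confidence intervals.
- Alongside, give per-arm counts of euploid embryos produced, transferred and still frozen, over all randomized cycles.
- Label any between-arm comparison that is kept as exploratory and non-randomized. If the full protocol says how the transferred embryo is determined when both dishes yield one, cite that text.
- Reword the Abstract's Discussion so that efficacy conclusions rest on the euploid rate, and add to the limitations in the main Discussion that the clinical endpoints are not randomized comparisons.
- Reconcile the Abstract's account of randomization with Trial design {8}.

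**Cost.** The trial gives up a confirmatory p-value for pregnancy outcomes that the design cannot support. No new data or change in care is needed. A change of analysis method does need ethics approval and a registry update under {25}. The Trial status section says the manuscript was submitted before data analysis ended and that no post hoc changes were made, so the change should be dated and declared openly.
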